# 1. STUDY BACKGROUND AND OBJECTIVES

## 1.1 BACKGROUND

Type 1 diabetes mellitus (T1D) results from autoimmune destruction of the insulin-producing pancreatic beta cells. Despite exogenous insulin therapy via daily insulin injections or insulin pump usage, individuals with T1D develop severe complications such as cardiovascular and renal disease, largely due to recurrent excessive fluctuations in blood glucose levels, referred to as dysglycemia,^1^ and the subsequent development of insulin resistance.^2–17^ These complications impact the quality of life and lifespan of those with T1D; estimated at fifteen years less than those without T1D.^18^

Contractility, morphology, metabolism, and the coordination of myocytes (muscle cells) with their surrounding microvascular and neuromuscular network are key characteristics of skeletal muscle, the organ system primarily responsible for our physical and metabolic capacities. The maintenance of this multitude of components and characteristics (collectively referred to as skeletal muscle health) is important for our overall well-being, with improvements in skeletal muscle health affecting blood glucose management, insulin sensitivity, cardiovascular outcomes (blood pressure regulation and oxygen transport), and the capacity to undertake activities of daily living.^19–25^ **While these statements are well-established for healthy individuals, our understanding of the impact of T1D on collective skeletal muscle health is limited, and the benefits of exercise training on T1D skeletal muscle health are virtually unknown.**

New data published by our lab highlights impairments in skeletal muscle metabolism, microvasculature, and function with T1D.^26–29^ Preliminary findings also suggest that a higher intensity or volume of exercise prescription may be warranted in those with T1D to maintain or improve muscle health relative to matched non-T1D counterparts. This is concerning, however, as current exercise recommendations for those with T1D are the same as for those without T1D.

## 1.2 OBJECTIVES

To come to a thorough understanding of the integrated impairments to skeletal muscle health and its coordinated response to exercise training in T1D, we will investigate the following specific three objectives. A brief methodological overview is provided with each objective, and methodological details may be found in Section 3 – Study Design and Measurement Instruments, below.

**Objective 1: Define the impact of T1D on systemic and muscle health**.

During a baseline period, study participants will undergo strength/aerobic fitness testing, body composition, blood analysis, glucose/activity/heart rate monitoring, muscle biopsy, neuromuscular assessments, and assessments of macrovascular and microvascular structure and function.

*Metric results acquired from visits 1/2 (see Section 3.1 Study Summary, below), will be compared between individuals with T1D and matched controls.*

**Objective 2: Identify the effects of exercise on systemic and skeletal muscle health in T1D.**

Following Objective 1, subjects will undergo a combined aerobic and resistance training program for twelve weeks. All tests from Objective 1 will be repeated.

*Metric results acquired from visits 1/2 (see Section 3.1 Study Summary, below), will be compared to metric results acquired from visit 3 for all individuals.*

**Objective 3: Determine the impact of detraining on systemic and muscle health in T1D.**

Following Objective 2, all subjects will undergo a detraining period consisting of unilateral knee-bracing for seven days, after which all tests from Objective 1 will be repeated. Subjects will then resume the combined aerobic and resistance training program for four weeks, after which all tests from Objective 1 will again be repeated.

*Metric results acquired from visit 3 (see Section 3.1 Study Summary, below), will be compared to metric results acquired from visit 4 for all individuals. Similarly, metric results acquired from visits 3 and 4 will also be compared to metric results acquired from visit 5 for all individuals.*

# 2. STUDY POPULATION, INCLUSION, AND EXCLUSION CRITERIA

## 2.1 STUDY POPULATION

Young (**18 to 30 years**) and older (**45 to 65 years**) adult females and males with and without confirmed T1D will be recruited to participate in this proposed investigation. All adults with T1D and without T1D will be matched for age, sex, and BMI at study onset. Subjects will also be matched for medication use, particularly statin and blood pressure medications. Participants must complete a standard medical questionnaire and physical activity readiness questionnaire (PARQ+) at study onset. Subjects should be sedentary or recreationally active, as defined by self-reported activity levels below the recommended 150-minute minimum of moderate-to-vigorous intensity physical activity per week, as recommended by Health Canada and Diabetes Canada.

## 2.2 EXCLUSION CRITERIA

Subjects will not be eligible to participate in or will be released from this study if they match any one of the following criteria:

- Chronic use of anti-inflammatory, glucocorticoid, or other pain-relief medication
- History of daily cannabis, tobacco, or nicotine use within six months of study initiation
- Have prediabetes
- Have type 2 diabetes
- Have health conditions that put the subject at risk to participate in exercise during this study
- Have atypical or Grade 2b diabetic sensorimotor polyneuropathy
- Have had more than one lifetime event of hospitalization for diabetic ketoacidosis

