## 3.2 DETAILS OF INITIAL STUDY DOCUMENTATION

Prior to the baseline study visit, all subjects will complete the following surveys / documents / tests to confirm their eligibility and suitability to participate in this investigation:

1. Standard medical questionnaire
2. CSEP Get Active Questionnaire and CSEP Get Active Reference Document
3. Global Physical Activity Questionnaire (GPAQ)
4. Seven-day food log
5. Informed consent form
6. Tissue consent form

All information acquired from phone calls or emails sent to interested participants prior to completing the documents above will be kept strictly confidential. Participants will be encouraged to contact any of the investigators if they have any questions or concerns about the study. A copy of all signed consent forms will also be added to each participants data file.

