**STRENGTH AND AEROBIC FITNESS TESTING**

- Muscle strength testing: Quadricep maximal isometric strength (maximal voluntary contraction; MVC) will be measured using an isometric dynamometer (Biodex). The protocol will consist of three five-second periods during which participants will be encouraged to maximally push against the padded lever strapped to their leg, with 30 second breaks between each repetition. The lever will be set to a knee joint angle of 90 degrees. Hand grip strength will also be tested using a hand grip dynamometer connected to a commercially available data acquisition unit (Powerlab). Bilaterally, participants will perform two MVCs on the handgrip dynamometer, and if the two measurements differ by 5% on the same hand, a third will be performed.
- Aerobic fitness testing: Depending on the success of the CSEP Get Active Questionnaire, a PWC130 or VO_2_Peak stationary bike test (Lode, Excalibur Sport) will be conducted to assess whole body aerobic fitness and exercise capacity. For individuals that answer “Yes” to any questions of the CSEP Get Active Questionnaire, and successfully complete the CSEP reference document, a PWC130 test will be performed: participants will complete two consecutive six-minute rides on a stationary bike. The resistance during these rides will have been selected to produce a heart rate of approximately 100-110 beats per minute in the first ride, and approximately 130-140 beats per minute in the second ride. A tiered system (i.e., PWC140, PWC150) will be used if required. For individuals that answer “No” to all of the CSEP Get Active Questionnaire, a VO_2_Peak test will be performed: participants will complete a cycling program with an incremental increase in resistance until exhaustion. The warm-up period will consist of two minutes at 50 Watts, followed by an incremental increase of one Watt each two-seconds. Successful achievement of VO_2_Peak (ml/kg/min) is obtained, and testing will stop, when any of the following are met: participant heart rate reaches their predicted maximum, respiratory exchange ratio exceeds 1.1, or when volitional exhaustion is reached.

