**INTRAMUSCULAR MEASURES**

- Motor neuron evaluation: Non-invasive high-density surface electromyography (EMG; Sessantaquattro 64-channel EMG) will be used to determine changes in the neural control of muscle force production. Namely, motor unit properties such as recruitment threshold, discharge rate, and conduction velocity will be evaluated to identify possible alterations in the neural strategies regulating force production.

To begin, the skin over the quadricep will be shaved and cleansed. EMG signals will be initially recorded during a brief voluntary contraction during which a non-adhesive dry electrode will be moved over the skin to detect the location of the innervation zone and confirm muscle fiber orientation/direction. Surface EMG signals of the vastus lateralis will then be recorded with an appropriately positioned two-dimensional adhesive electrode grid whose cavities will be filled with conductive paste once affixed to the skin. A strap electrode will be dampened with water and positioned on the medial malleolus of the right leg to be used as a ground electrode. The EMG signals will be recorded in a mono-polar mode and converted to digital data through a multi-channel amplifier for evaluation and analysis.

- Microvascular function and perfusion will be evaluated within the quadricep (vastus lateralis) using the Contrast Enhanced UltraSound (CEUS) method.

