CEUS uses gas-filled lipid microspheres with thin permeable shells that are 1-3µm in size. Once the microspheres are released into systemic circulation (via intravenous infusion through a forearm vein), they act as acoustic reflectors to enhance the contrast in collected ultrasound images. The microspheres are smaller than red blood cells, which allows them passage through the microcirculation, but prevents them from diffusing through vessel walls. Their echogenic properties allow the quantification of the level of contrast within a tissue over time which indicates the overall perfusion capacity.^39^ This technique records the contrast-enhanced acoustic time-intensity curve at low mechanical index (MI) (MI = .8) during steady state intravenous microbubble infusion. Briefly, once steady state is achieved, a high MI “flash” (MI = 1.32) is implemented to destroy microbubbles in the region of interest, where microbubble replenishment curves are subsequently recorded using curve-fitting techniques. High MI “flashes” and subsequent low MI recordings will be performed for the assessment of microvascular blood flow and reactivity at rest and following unilateral isotonic knee extensions at 50% 1-RM, respectively.^48,49^ Sulfur hexafluoride-containing lipid microspheres (SonoVue; Bracco, Milan, Italy) are activated by a vial mixer (Vialmix, Lantheus) at 75Hz for 45 seconds, after which the activated microbubbles are prepared for intravenous infusion.^42^ Preparation of activated microbubbles is carried out by an experienced operator, strictly following the instructions provided by SonoVue. Infusion (2ml/min for one minute, then 1ml/min thereafter) and venous catheterization (antecubital vein) will be performed by a trained operator.

Microbubble appearance will be assessed within the quadricep muscles, and slope of bolus-muscle-perfusion, wash-in time, maximum acoustic intensity, and integral of peak intensity will be calculated from both legs to evaluate microvascular function. These measurements are also approved under the HiREB ethics protocol #8000.

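### The Section 2.2 list for ineligibility and release does not name pregnancy, although 36 women aged 18-30 are each budgeted five research DEXA scans and have repeated contrast ultrasound

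*Protocol*

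**What the plan says.** Protocol Section 2.2 sets a single rule for entry and for withdrawal: "Subjects will not be eligible to participate in or will be released from this study if they match any one of the following criteria". Seven items follow: long-term use of certain medicines; recent daily cannabis, tobacco or nicotine use; prediabetes; type 2 diabetes; exercise-risk conditions; a specified degree of neuropathy; and repeated ketoacidosis admissions. The item nearest to pregnancy is "Have health conditions that put the subject at risk to participate in exercise during this study".

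Screening is described in two places. Section 2.1 says "Participants must complete a standard medical questionnaire and physical activity readiness questionnaire (PARQ+) at study onset". Section 3.2 says "Prior to the baseline study visit, all subjects will complete the following surveys / documents / tests to confirm their eligibility and suitability", and then lists a medical questionnaire, the CSEP Get Active forms, an activity questionnaire, a food log and consent forms.

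The procedures concerned are these:

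- **DEXA.** Section 3.3 includes it under body composition, and Section 5 budgets five scans for each participant.
- **Contrast ultrasound.** Section 3.3, under intramuscular measures, says "Microvascular function and perfusion will be evaluated within the quadricep (vastus lateralis) using the Contrast Enhanced UltraSound (CEUS) method". The contrast is infused through a forearm vein. The same part adds "These measurements are also approved under the HiREB ethics protocol #8000".
- **Repetition.** After the twelve weeks of training, Objective 2 in Section 1.2 states "All tests from Objective 1 will be repeated". Objective 3 repeats the set after detraining and again after re-training.

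**The concern.** Young women are a planned stratum, and the study subjects them to repeated imaging for research purposes over 18 weeks. A woman may be pregnant at entry, or may conceive between visits. Section 2.2 is where the protocol says who may not enter and who must leave, and it is detailed enough to specify a neuropathy grade and a number of hospital admissions. On pregnancy it is silent.

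The list therefore does not say what happens to a woman who is pregnant but judged fit to exercise. Read literally, it would let her enter, or stay after conceiving, and go on to the next DEXA scan. What is at stake is participant safety and a decision that the protocol should make in advance. Eligibility and release rules belong in a protocol and are not something that a statistical analysis plan would be expected to supply.

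**Working it through.** **Inputs**

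- Section 2.3: 18 women aged 18-30 with T1D and 18 without; 24 women aged 45-65 with T1D and 24 without; 168 participants in all.
- Section 5: five DEXA scans per participant, $40 per scan, DEXA total $33,600.
- Section 1.2: the full test set at baseline and after training, detraining and re-training.
- Section 3.3, continuous monitoring: 18 weeks of study.

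**The plan's own figure.** Participants x scans x unit cost = 168 x 5 x $40 = $33,600. This equals the budget line, so five scans for every participant is a consistent reading.

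**Women concerned.** Aged 18-30: 18 + 18 = 36. Aged 45-65: 24 + 24 = 48. The protocol does not say how many of the 48 could conceive, so the range is 0 to 48.

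**Procedures.** DEXA scans budgeted in the younger women: 36 x 5 = 180. Older women who could conceive add between 0 and 48 x 5 = 240. Contrast ultrasound falls at four time points by the wording of the objectives. I give no session total, because baseline spans visits 1/2 and the visit schematic is not shown.

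**Could another part of the text settle the matter?**

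1. *The exercise-risk item in Section 2.2.* It applies at entry and, through the release wording, later as well. Its test is risk from exercise. It does not mention imaging or contrast, so it resolves the case only if the pregnancy is judged to make exercise unsafe.
2. *The screening forms.* Sections 2.1 and 3.2 place them at study onset or before the baseline visit. No later re-check of eligibility is described, so a form completed then cannot detect a later conception.
3. *The consequence of a positive answer.* Under strength and aerobic fitness testing in Section 3.3, a participant who answers Yes on the Get Active Questionnaire continues on this condition: "and successfully complete the CSEP reference document, a PWC130 test will be performed". A different fitness test is the only described result once that document is completed. The wording implies that completion can fail, but no consequence of failure is stated.
4. *Which form applies.* Section 2.1 names the PARQ+; Section 3.2 lists the Get Active forms and not the PARQ+. A reader cannot tell from the text which questions every woman is asked.

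**The case against.** The strongest reply is that this is an omission, and that the places most likely to fill it are not available here. The questionnaires were attached to the ethics submission, the consent pages and visit schematic are not shown, and the contrast measurements are also approved under a separate ethics protocol. The entry forms exist expressly to confirm suitability. The exercise-risk item could reasonably be applied to a pregnant woman facing interval training and a week on crutches with a braced knee, and releasing her would also end her scans.

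Much of this stands. Entry may well be covered by forms that I cannot see, and the exercise-risk item gives real discretion. What remains is that a question on a form is not a release rule, that no re-check after baseline is described, and that the text links HiREB protocol #8000 to the contrast and flow-mediated dilation measurements but not to DEXA.

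Stronger readings are tempting, and the document does not support them:

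- *That the study has no safeguard for pregnancy.* The unseen documents may contain one.
- *That the decision rests with a single investigator.* Nothing in the protocol says who decides.
- *That the contrast agent carries a particular risk in pregnancy.* The protocol gives no such guidance, so a check before infusion is proposed only as a precaution.
- *That 180 scans measures exposure in pregnancy.* It counts budgeted scans in all the younger women.

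**Conclusion.** The point holds as a gap in the governing list. Section 2.2 does not name pregnancy as a ground for exclusion or release, while 36 women aged 18-30, and between 0 and 48 older women who could conceive, are each budgeted five DEXA scans and have contrast ultrasound repeated after each phase.

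The conclusion rests on two assumptions: that Section 2.2 is applied as written, and that pregnancy status is relevant before a research DEXA scan. The second is general knowledge of DEXA as an X-ray method; the protocol gives no dose. The document contains no pregnancy rate, so no number of affected women can be given, and I do not claim that harm will occur. There is no claimed effect on estimates, power or event counts. Confidence is medium, because unseen study documents may already deal with part of this. The change is worth making because it could alter who is enrolled and who is scanned, at very little cost.

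**What to change.** 1. Add *pregnant* to Section 2.2, so that it operates both as an exclusion and as a release criterion.
2. In Section 3.3, have women who could be pregnant confirm their status before each DEXA scan and, as a precaution, before each contrast infusion. Leave the method to the investigators and the ethics board.
3. If the questionnaires, consent forms or HiREB protocol #8000 already cover this, make Section 2.2 agree with them or refer to them there.

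The cost is one added criterion, one question per visit for the women concerned, and possibly some women excluded or released.

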## 2.3 SAMPLE SIZE

We will include a total of **168 participants** in the current investigation – 84 participants with T1D, and 84 participants without T1D. Please see a breakdown of sample size by sex and age in the chart below. Groups are stratified in this way to ensure that appropriate comparisons between subjects with T1D and without T1D, overall AND stratified by young adult / older adult, as well as sex, may be made.

| Cohort | Age Group | Females | Males |
| --- | --- | --- | --- |
| T1D adults aged **18-30** (T1D duration <20 years) | Young adult | 18 | 18 |
| T1D adults aged **45-65** (T1D duration >30 years) | Older adult | 24 | 24 |
| Non-T1D adults aged **18-30** | Young adult | 18 | 18 |
| Non-T1D adults aged **45-65** | Older adult | 24 | 24 |

Power Calculation: Statistical analysis parameters were developed to allow sufficient power of Objective 1 primary outcome measures (the effect of T1D on skeletal muscle and microvascular health). Power calculations (2-sided test, power=0.8, alpha=0.05) were conducted using recently published and collected data from our lab. For Older adult subjects, mitochondrial density values (^26^; mu1 6.293, mu2 4.290, sigma 1.395) were used to reveal sufficient sample size for statistical power as n=17/sex/group. For Young adult subjects, Pax7-positive nuclei per 100-myofibers (indicative of skeletal muscle satellite cell content; preliminary data not shown herein; mu1 17.29, mu2 13.86, sigma 3.08) were used to reveal sufficient sample size for statistical power as n=13/sex/group. Both values were increased to a final sample size of older adult: n=24/sex/group and young adult: n=18/sex/group to provide a 40% excess to account for attrition and variability in initial aerobic fitness and responses to exercise training (exercise data was not available to derive appropriate power calculations). A full breakdown between groups can be seen in the table above. The longitudinal and paired nature of our methods further strengthens our statistical power for pre- and post- intervention analyses.

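### The older-adult sample size of 17 per sex per group does not follow from its printed inputs, which give 9, so the 24 versus 18 split does not follow from the stated calculation

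*Protocol*

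**What the plan says.** All the material is in one paragraph of protocol section 2.3. The common settings are "Power calculations (2-sided test, power=0.8, alpha=0.05". For older adults, based on mitochondrial density, the inputs and the result are given as "mu1 6.293, mu2 4.290, sigma 1.395) were used to reveal sufficient sample size for statistical power as n=17/sex/group". For young adults, based on satellite cell content, the inputs are "mu1 17.29, mu2 13.86, sigma 3.08", and these "were used to reveal sufficient sample size for statistical power as n=13/sex/group". A 40% excess is then added: "Both values were increased to a final sample size of older adult: n=24/sex/group and young adult: n=18/sex/group". The cell sizes in the table, the 84 per diabetes group and the total of 168 follow from those two numbers.

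The section names no formula or software and states no multiplicity adjustment. Section 4 names the baseline comparison as a t-test, or a Mann-Whitney U test if the data are not normal.

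**The concern.** With the same test, alpha and power, a larger standardised difference needs fewer participants. Section 2.3 shows the reverse: the cohort with the larger planned effect has the larger n. That can be seen without software, and it means that at least one printed figure for the older cohort is wrong or incomplete.

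The figure of 17 fixes the 24 per older cell, and so 96 of the 168 participants (24 × 4 cells). Section 2.3 is the only sample-size rationale in the protocol. Participants are asked for muscle biopsies, 12 weeks of training, seven days of single-leg immobilisation and re-training with repeated testing. A reader should be able to see how their number was reached, and for the older cohort cannot.

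**Working it through.** **Inputs (section 2.3).** Two-sided alpha 0.05, power 0.80, equal groups.
- Older: means 6.293 and 4.290, SD 1.395. Difference 2.003, so d = 2.003 / 1.395 = 1.436.
- Young: means 17.29 and 13.86, SD 3.08. Difference 3.43, so d = 3.43 / 3.08 = 1.114.

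**Formula.** By normal approximation, n per group = 2(1.960 + 0.842)² / d² = 15.70 / d². The t-test figure comes from the noncentral t distribution.

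**Young adults, the figure that reproduces.** 15.70 / 1.114² = 12.66, so 13 per group, as stated. The t-test calculation gives 13.69, so 14.

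**Older adults, same method.** 15.70 / 1.436² = 7.61, so 8 per group. The t-test calculation gives 8.69, so 9. The stated figure is 17.

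**Power on the printed inputs (t-test).**

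| n per group | Older (d = 1.436) | Young (d = 1.114) |
|---|---|---|
| 9 | 81.6% | 60.2% |
| 13 | 94.0% | 77.8% |
| 17 | 98.2% | 88.3% |
| 18 | 98.7% | 90.1% |
| 24 | 99.8% | 96.5% |

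**Other readings of the older-adult calculation (n per group).**
- Paired t-test: 6.
- One-sided alpha 0.05: 6 to 7.
- Mann-Whitney efficiency correction: 10 to 11.
- Alpha halved to 0.025: 11 (10.58).
- Power 0.90: 11 to 12.
- Power 0.95: 13 to 14.

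A figure of 17 can be forced by combining a much smaller alpha with higher power (for example alpha 0.01 with power 0.90 gives 16.18, so 17), by multiplying the SD by √2 (16.2, so 17), or by taking roughly the total over both groups (2 × 8.69 = 17.4). None of these matches the stated settings or the per-group wording, and none is the basis that reproduces the young-adult 13.

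**What would make 17 right.** At 80% power, 17 per group detects d = 0.991. With the printed difference, the SD would have to be 2.003 / 0.991 = 2.02 (2.08 by normal approximation). With the printed SD, the difference would have to be 0.991 × 1.395 = 1.38.

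**Carrying the 40% excess forward.** 17 × 1.4 = 23.8, so 24, and 13 × 1.4 = 18.2, taken as 18; both match the table. From 9 the same rule gives 9 × 1.4 = 12.6, so 13 per older cell.

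**The case against.** The strongest defence is that nothing is put at risk. A reader might infer from the failed arithmetic that the older cohort lacks its stated 80% power. The protocol does not support that. On the printed inputs, power is 98.2% at 17 and 99.8% at 24. If the SD is the misprint and is really about 2.02, power is 80% at 17 and about 92% at 24. On either of these explanations, planned enrolment meets the target for the sizing outcome. This part of the defence stands.

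A reader might also infer that 44 older participants are surplus, since (24 − 13) × 4 = 44. That holds only if the printed means and SD are right, which cannot be checked without the source study. It also treats one baseline outcome as the sole purpose of the sample. Section 2.3 wants comparisons overall, by age and by sex, and says that no exercise data were available for a power calculation; section 4 plans interaction terms for sex. The number shows an excess over the single-outcome calculation, not over the needs of the study. For the same reason, moving places from older to young cells would be premature.

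The young-adult figure is not a second error. Thirteen against 14 is a choice between normal approximation and t-test, and the 18 planned give 90.1%.

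What the defence does not answer is the mismatch itself. Section 2.3 assigns the allowance for attrition and for variability in fitness and training response to the 40% excess, not to the 17, so those needs cannot explain why 17 is presented as the result of these inputs.

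**Conclusion.** The point holds as an arithmetic error in the older-adult calculation. The printed inputs give 9 per sex per group by t-test, or 8 by normal approximation; the protocol states 17. The young-adult figure reproduces at the stated settings, so the two cohorts were not sized on the same basis, and the 24 versus 18 split has no support in the calculation offered for it.

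The consequence depends on which figure is wrong, and the protocol does not show that. If the means and SD are right, the error is conservative and the stated rule leads to 13 rather than 24 per older cell. If 17 is right, a mean or the SD is misreported. Entry of a both-groups total as a per-group n is one possible cause, but it is a guess. These results assume a two-sample comparison with equal groups and a common SD.

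**What to change.** Re-run the older-adult calculation and name the formula or software used for both cohorts. Then correct whichever figure is wrong.

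- **If a mean or the SD is misreported**, print the correct value and confirm that it gives 17 at alpha 0.05 and power 0.8.
- **If the inputs stand**, restate the result: 9 per sex per group reaches 80% power (81.6%), 17 gives 98% and 24 gives 99.8%; at 80% power, 17 detects d = 0.99 and 24 detects d = 0.83. Then justify keeping 24 per cell, and so 168 in total, on grounds that apply, such as the sex-stratified and interaction analyses or the training and detraining objectives.

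The cost is one re-run and a rewording of section 2.3. Leave the total and the allocation between cohorts unchanged until the source of the error is known.
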